#### Rumination

Rumination will be measured by the Ruminative Responses Scale (RRS). The scale was developed by Nolen-Hoeksema [55], and the Chinese version was revised by Han Soo [56] et al. The scale consists of 3 dimensions, namely, symptom rumination, compulsive thinking, and reflective rumination, with a total of 22 items. The scale is scored on a 4-point scale, with higher scores indicating more severe ruminative thinking. The scale is widely used in China and has good reliability and validity, with reliability coefficients ranging from 0.76 to 0.89 for each dimension.

#### Social engagement

The purpose of assessing social engagement in this study is to avoid confounding the effects of social engagement and reminiscence therapy on depressive symptoms in older adults. Social engagement will be measured by the Chinese version of the Impact on Participation and Autonomy Questionnaire (IPA). This scale was developed by Cardol [57] et al. and measures the individuals’ own perceived social engagement. In this study, the Chinese version of the IPA, which was revised and adapted for use in Chinese populations by Li Hong et al. [58] et al. was employed, including 25 items in four dimensions: indoor autonomous participation (7 items), family role (7 items), outdoor autonomous participation (5 items), and social life (6 items). Each item was rated on a 5-point Likert scale, with “a lot” being assigned a score of 0 and “very little” being assigned a score of 4. The higher the score, the worse was the level of social engagement.

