**Methods:**

In this multicentre, single-blind, three-arm parallel randomized controlled study, we aim to enrol 78 older adults aged 65 years or older with a score of ≥ 11 on the Geriatric Depression Scale, and participants will be randomly assigned to either a reminiscence therapy group, a reminiscence therapy with memory specificity training group or a usual care group. Assessments will be conducted at baseline (T0) as well as immediately post-intervention (T1) and 1 (T2), 3 (T3) and 6 (T4) months post-intervention. The primary outcome measure is self-reported depressive symptoms, measured using the GDS. Secondary outcome measures include measures of autobiographical memory, rumination, and social engagement.

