Reminiscence therapy, as a potential psychological intervention to improve depressive symptoms in older adults, has an important therapeutic aspect of enhancing autobiographical memory and is often used interchangeably in the literature due to its similarity to the term “life review intervention” [24]. It enhances older people’s positive affect [25], cognitive functioning [26], social participation [27], quality of life, and ability to adapt to ageing [28] through the recall, narration, and reflection of past experiences. In addition to previous meta-analyses showing the significant effect of reminiscence-based interventions in improving psychological problems and enhancing well-being in older adults [29–31], there are also empirical studies showing that when researchers guided older adults through interventions for reminiscence at different stages of life, the older adults became more resistant to social stress, increased their ability to think and act for themselves, and finally, experienced completeness in the final stages of life [32–34]. However, in terms of the improvement of autobiographical memory, studies have shown that reminiscence therapy is not effective in improving it [35–37], possibly because reminiscence therapy is an inherent normative process of thinking about the past [38], rather than the practice and improvement of specific event details, which cannot significantly improve the effect of autobiographical memory.

Memory-specific training (MeST), as an intervention for improving autobiographical memory in some patients with mood disorders, has a good effect on patients’ difficulties in recalling personal events through the use of clues to recall words. Although MeST is simple and can be implemented singly, the effect is not good [39, 40]; thus, it can also be implemented together with traditional interventions such as reminiscence therapy as an adjunct therapy [40]. Consequently, there have been many studies combining these two therapies.

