Currently, reminiscence therapy combined with memory-specific training is mainly used in the psychological treatment of cancer patients in palliative care, and its effectiveness needs further validation, as randomized controlled trials of Life Review Therapy combined with Memory Specificity Training (LRT- MST) by Gitta Kleijn showed no significant differences between the two groups in terms of anxiety, depression, quality of life and autobiographical memory in cancer patients [41, 42]. However, other studies have shown that reminiscence therapy based on autobiographical memory training can be used in future studies to investigate available, cost-effective, low-intensity treatment options for patients experiencing mood disorders [43, 44]; thus, further investigation of this therapy is warranted.

Based on the national situation that depressed older people are increasing year by year in China, this study aims to implement a randomized controlled trial of reminiscence therapy combined with memory specificity training in a Chinese context to investigate whether this therapy can reduce rumination and improve depressive symptoms in older people and improve their psychological health by improving autobiographical memory. In this study, it is hypothesized that older people who participate in reminiscence therapy combined with memory specificity training will report improved autobiographical memory specificity, less rumination, and significantly lower levels of depressive symptoms at postintervention and follow-up time points than older adults receiving usual care and reminiscence therapy alone; we further hypothesize that these improvements will be maintained for 6 months after the intervention.

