### Outcome measures

See Table 4 for an overview of all measurement instruments and timepoints for older people.

**Table 4 Tab4:** Overview of instruments per assessment

Measures	T0	T1	T2	T3	T4	
Demographics	×					
GDS	×	×	×	×	×	
ATM	×	×	×	×	×	
RRS	×	×	×	×	×	
IPA	×	×	×	×	×	
T0: baseline, T1: immediately postintervention, T2: 1month postintervention, T3: 3 months postintervention, T4: 6 months postintervention.						

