### Statistical analysis

A database will be established using EpiData, and the data will be entered by two persons and analysed statistically using SPSS 26.0 software. The measurement data such as scale scores will be expressed as the mean ± standard deviation (x ± s). Count data such as general demographic data will be described by the frequency and percentage. The status of each scale score before and after the intervention within each group and the measurement data between multiple groups will be analysed by repeated-measures ANOVA and simple effects analysis if they are normal and have equal variance, and the statistics will be described by median and mean difference (MD). For measures with skewed distribution, median and quartiles will be used to describe the statistics, and Kruskal‒Wallis multiple comparisons will be used to compare the data between and within groups. Intention-to-treat will be used to process the data and P < 0.05 will be considered statistically significant.

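### Social engagement is measured to avoid confounding, but the stated analysis delivers no such control, and only its baseline score could serve that purpose

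*Protocol article*

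**What the plan says.** The protocol article gives social engagement two roles and an analysis that serves only one of them.

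- **Social engagement section:** "The purpose of assessing social engagement in this study is to avoid confounding the effects of social engagement and reminiscence therapy on depressive symptoms". No other purpose is given there.
- **Abstract, Methods:** "Secondary outcome measures include measures of autobiographical memory, rumination, and social engagement".
- **Background:** among the things that reminiscence therapy is said to enhance are "cognitive functioning [26], social participation [27], quality of life".
- **Outcome measures, Table 4:** the IPA is taken at every visit, like the other scales. The visits are "T0: baseline, T1: immediately postintervention, T2: 1month postintervention, T3: 3 months postintervention, T4: 6 months postintervention".
- **Statistical analysis:** scale scores "will be analysed by repeated-measures ANOVA and simple effects analysis if they are normal and have equal variance". For skewed measures, Kruskal-Wallis "multiple comparisons will be used to compare the data between and within groups". No covariate, adjusted model or mediation analysis is mentioned.
- **Background, hypotheses:** participants in the combined arm "will report improved autobiographical memory specificity, less rumination, and significantly lower levels of depressive symptoms". Social engagement is not among the hypotheses.

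Two design features matter here. Both active arms meet in groups of six or seven residents, once a week for four weeks, 90 minutes each time; usual care is given to everyone and includes no matching meetings. The Randomization and blinding section lets an envelope decide which of three homes delivers which intervention, although Study Design speaks of participants being divided at random.

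**The concern.** Measuring a variable does not control for it. If social engagement is to be kept from confounding the treatment effect on depressive symptoms, it has to enter the design or the model, and it has to be measured before treatment. The stated purpose mentions neither a time point nor a model, and the stated analysis uses the IPA only as one more scale to compare.

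Two things are at stake. First, a report could claim that social engagement was dealt with when it was not, although with allocation by home the arms may well differ in engagement at the start. Second, someone who later tries to honour the stated purpose has five IPA scores to choose from, four of them taken after treatment. Those four may carry part of the treatment effect, by the protocol's own account of what reminiscence does.

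**Working it through.** No figure in the protocol bears directly on this point, so the check is mainly a comparison of the sections.

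**Step 1. Can the stated analysis deliver the stated purpose?** Repeated-measures ANOVA is described without a covariate, and Kruskal-Wallis cannot take one. Under either, the GDS contrast is unadjusted and the IPA is analysed separately. The control does not happen.

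**Step 2. Could T1 to T4 IPA deliver it?** A confounder must not be a consequence of treatment. The Background expects reminiscence to raise social participation, and each active-arm resident receives 4 × 90 = 360 minutes (6 hours) of group contact that usual care lacks. Post-intervention IPA is therefore an outcome and a possible mediator.

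**Step 3. Could T0 IPA deliver it?** It precedes treatment, so adjusting for it removes no treatment effect. It is relevant because homes may differ in engagement: 78 / 3 = 26 per arm, which equals the 26 residents sought per home, so the numbers fit one home per arm. In that case arm and home coincide, and T0 IPA can adjust for a measured difference between residents but cannot separate arm from home.

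**Step 4. Illustration of why the time point matters.** The protocol gives no effect of treatment on IPA or of IPA on GDS, so these are assumed. All effects are in SD units, in the direction of improvement.

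- Total effect on GDS: 0.8. This is the effect size in Sample size calculation, taken here as a standardized mean difference, which the protocol does not specify.
- b, change in GDS per SD of IPA: 0.4 (assumed).
- a, effect of treatment on IPA: 0.2, 0.4 or 0.6 (assumed).
- Correlation of T0 and post-intervention IPA: 0.6 (assumed).

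Effect left after adjusting for post-intervention IPA = 0.8 − a × b:

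- a = 0.2: 0.8 − 0.08 = 0.72
- a = 0.4: 0.8 − 0.16 = 0.64
- a = 0.6: 0.8 − 0.24 = 0.56

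A simulation of two arms of 24 (individual allocation, no home effect, two-sided 5% test, 4000 runs) gave these mean estimates, with power in brackets:

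| a | no adjustment | T0 IPA | post-intervention IPA |
|---|---|---|---|
| 0.2 | 0.802 (0.774) | 0.801 (0.797) | 0.727 (0.752) |
| 0.4 | 0.794 (0.765) | 0.806 (0.798) | 0.647 (0.630) |
| 0.6 | 0.795 (0.764) | 0.805 (0.790) | 0.564 (0.501) |

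Over a wider assumed range (a from 0.3 to 0.7, b from 0.3 to 0.5), the part removed runs from 0.3 × 0.3 = 0.09 to 0.7 × 0.5 = 0.35 SD, or 0.09 / 0.8 = 11% to 0.35 / 0.8 = 44% of the effect. The last column of the table and this range describe an analysis that the protocol does not plan. The unadjusted power falls short of the 0.90 in Sample size calculation under this two-sample test; that is a separate matter.

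**The case against.** **The article is a summary.** A journal article may leave covariates to a full protocol or analysis plan that is not shown, and such a document could name T0 IPA. This stands, and the point should not rest on a missing detail. It rests on printed text: one section calls the variable a confounder to be kept apart, two others treat it as something that treatment changes, and the analysis that is printed gives it no controlling role.

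**No one plans to adjust for post-intervention IPA.** This also stands. A reader might infer that the primary GDS contrast is biased by over-adjustment, or that the stated control must either fail to happen or consume treatment effect. The documents support neither. The planned analysis has no adjustment, T1 to T4 IPA is scheduled as for every other scale, and baseline adjustment is a third course that does no harm. A large treatment effect on the IPA is not assured either: only 6 of its 25 items concern social life.

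**Confounding by engagement is a reasonable worry.** Agreed. With interventions assigned by home, baseline differences are plausible, so the protocol's purpose is sensible and only its execution is lacking.

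**Usual care is a legitimate comparator.** It is, and the hypotheses claim superiority over it without claiming to isolate reminiscence from contact. What remains is that the Social engagement section implies such a separation, which measuring the IPA does not achieve.

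**RT-MeST versus RT looks free of the problem.** A reader might infer this because both arms share the session format. Under the Randomization and blinding section it is still a comparison of homes. The added prompts also ask about related activities and about repeating them, which could themselves alter participation.

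**Conclusion.** The point holds in a limited form. The purpose given for the IPA is not served by the analysis stated, and T1 to T4 scores could not serve it because treatment may change them. T0 IPA could serve it in part.

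No bias in the planned GDS analysis has been shown, and none can be sized from the documents. The attenuation figures are illustrative, rest on assumed path values, and apply only if post-intervention IPA were used as a covariate. They are a reason to rule that use out and do not describe the plan.

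The concern about baseline imbalance depends on allocation by home. If residents were allocated individually, as Study Design suggests, imbalance would be due to chance, and T0 adjustment would serve mainly precision. The fix is sound under either reading. Under allocation by home, it leaves the confounding of arm with home untouched.

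**What to change.** 1. Reword the Social engagement section: T0 IPA is a baseline covariate, and T1 to T4 IPA is a secondary outcome.
2. Adjust the GDS analysis for T0 IPA in a model that accepts a covariate, such as repeated-measures ANCOVA or a linear mixed model. If baseline GDS stays in as one of the repeated levels, include T0 IPA by visit; otherwise the covariate drops out of the change-from-baseline contrasts. Kruskal-Wallis can remain as an unadjusted sensitivity analysis.
3. Analyse T1 to T4 IPA only as a secondary outcome or in a labelled exploratory mediation analysis, and state that the treatment effect on GDS will not be adjusted for it.
4. State that either active arm against usual care estimates the whole effect, including group contact. State that RT-MeST against RT is matched for session format and contact but is still a comparison of homes if interventions are assigned by home, and that T0 IPA adjustment cannot remove confounding between homes.

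The cost is a few sentences, one covariate that is already collected, and the few degrees of freedom it uses. The claim against usual care becomes more modest.

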### Statistical analysis

A database will be established using EpiData, and the data will be entered by two persons and analysed statistically using SPSS 26.0 software. The measurement data such as scale scores will be expressed as the mean ± standard deviation (x ± s). Count data such as general demographic data will be described by the frequency and percentage. The status of each scale score before and after the intervention within each group and the measurement data between multiple groups will be analysed by repeated-measures ANOVA and simple effects analysis if they are normal and have equal variance, and the statistics will be described by median and mean difference (MD). For measures with skewed distribution, median and quartiles will be used to describe the statistics, and Kruskal‒Wallis multiple comparisons will be used to compare the data between and within groups. Intention-to-treat will be used to process the data and P < 0.05 will be considered statistically significant.

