### Participants

#### Eligibility and recruitment

Participants will be recruited from all three nursing homes simultaneously.

Once a nursing home has a sample of 26 subjects, they will proceed to the next step. Inclusion criteria are age ≥ 65 years; nursing home residence ≥ 3 months; Geriatric Depression Scale score ≥ 11; Mini-mental State Examination score ≥ 21; and voluntary participation in this study. Exclusion criteria include the acute onset of major illnesses such as cardiac, respiratory, digestive, or neoplastic disease; the development of a psychological illness other than depression; the taking of antidepressants or psychotropic drugs; an imminent discharge from a nursing home involved in the study; and receipt of other psychological treatment within the past 3 months.

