#### Depressive symptoms in older people

Depressive symptoms in older people will be measured by the Geriatric Depression Scale. This scale was developed by Yesavage [50] et al. as a special depression screening scale for people over 56 years of age, and each examination takes approximately 15 min. It consists of 30 questions and four factors: ① unhappiness ② apathy and anxiety ③ loss of hope and morale ④ memory loss and reduction of social activity. Ten of the 30 items are scored in the reverse direction and 20 in the positive direction. The total score is 0–30, with higher scores indicating more severe depression. Scores of 0–10 are normal, scores of 11–20 indicate mild depression, and scores of 21–30 scores indicate moderate and severe depression. The Cronbach coefficient of the GDS is > 0.85, the retest reliability is > 0.73, and the reliability is > 0.84, with good internal consistency and stability [51].

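### Within-arm before-after tests on a GDS that residents had to score 11 or more on to enter can show a 'significant' fall by regression to the mean, if the qualifying score is also T0

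*Protocol article*

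**What the plan says.** - **Entry.** Eligibility and recruitment requires "Geriatric Depression Scale score ≥ 11; Mini-mental State Examination score ≥ 21". The section on depressive symptoms places 11 at the lower edge of mild depression.
- **Outcome.** The abstract states: "The primary outcome measure is self-reported depressive symptoms, measured using the GDS".
- **Reliability.** For the GDS, "the retest reliability is > 0.73". This is a lower bound only.
- **Analysis.** One sentence of the Statistical analysis section covers both "The status of each scale score before and after the intervention within each group" and, directly after it, "the measurement data between multiple groups will be analysed by repeated-measures ANOVA and simple effects analysis". The rank-based alternative for skewed data likewise covers comparisons between and within groups. One threshold applies to everything: "P < 0.05 will be considered statistically significant".
- **Hypothesis.** The Background compares the combined arm with usual care and with reminiscence therapy alone, then adds: "we further hypothesize that these improvements will be maintained for 6 months after the intervention".
- **Assessments.** Table 4 lists the GDS at T0 to T4. The article does not describe a screening GDS distinct from T0.
- **Allocation.** Study Design says participants are randomised 1:1:1. Randomization and blinding says envelopes decide which nursing home delivers which intervention.

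**The concern.** Scores selected for being high on one occasion are, on average, lower on the next, with no treatment at all. When the selecting score is also the baseline of a before-after test, that test measures regression to the mean together with any real change.

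The plan gives the within-arm test the same threshold as the between-arm test and does not rank them. A reader of the results could therefore take a significant fall within an arm as evidence that the intervention works. Under the simple error model used below, the regressed mean stays at its new level at T1, T2, T3 and T4, so a within-arm reading would also appear to show an improvement that lasts six months.

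**Working it through.** The plan gives no figure on this point, so there is none to reproduce. The check asks how often a within-arm T0 versus T1 test is significant in the direction of improvement when nothing has changed.

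**Inputs from the article:** cut-off 11; retest reliability r above 0.73; alpha 0.05 (sidedness not stated, two-sided assumed, so 0.025 in the direction of a fall); 24 evaluable per group; 78/3 = 26 enrolled per group.

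**Assumed, not in the article:** screened-population mean GDS 7–11 and SD 5–6; normal scores, with a check on whole-number scores from 0 to 30; true score plus independent error; r of 0.85 and 0.90 as alternatives; a paired t-test standing in for the simple effect within an arm.

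**Formulas.** With c = (11 − mean)/SD and λ = φ(c)/(1 − Φ(c)):
- mean qualifying score = mean + SD × λ
- expected untreated fall = (1 − r) × SD × λ
- SD of change = SD × √[(1 − r)²(1 + cλ − λ²) + 1 − r²]

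**Worked case, mean 9, SD 6, r = 0.73.**
- c = 2/6 = 0.333; λ = 0.3774/0.3694 = 1.0215
- qualifying mean = 9 + 6 × 1.0215 = 15.1
- fall = 0.27 × 6 × 1.0215 = 1.65 points
- SD of change = 6 × √(0.0729 × 0.297 + 0.4671) = 4.2
- noncentrality = 1.65/4.19 × √24 = 1.93 for n = 24, and 2.01 for n = 26
- chance of a significant fall: 0.46 (n = 24) or 0.49 (n = 26)

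**Ranges from simulation** (n = 24 and 26, continuous and whole-number scores):

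| Assumed screened population | r = 0.73 | r = 0.85 | r = 0.90 |
|---|---|---|---|
| Mean 7–11, SD 5–6; qualifying GDS is T0 | 0.27–0.74 | 0.16–0.48 | 0.13–0.34 |
| Mean 13, SD 5–6 (about two thirds above the cut-off); qualifying GDS is T0 | 0.15–0.20 | 0.10–0.13 | 0.08–0.10 |
| Any of these; T0 is a fresh reading after qualifying | about 0.025 | about 0.025 | about 0.025 |

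Across the first row the expected fall is about 1.1–2.1 points at r = 0.73 and 0.6–1.1 at r = 0.85. The upper end at r = 0.90 comes from mean 7, SD 5, n = 26: λ = 1.367, fall = 0.1 × 5 × 1.367 = 0.68, SD of change 2.19, noncentrality 0.68/2.19 × √26 = 1.59.

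**Between arms.** With individually randomised arms, the same no-effect simulations gave a type I error of 4.6–5.2% for a between-arm test of change. The expected fall is equal in every arm and cancels.

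**If whole homes are allocated.** Homes with different GDS levels regress by different amounts. With SD 5 and r = 0.73, a home with mean 7 would fall by 0.27 × 5 × 1.367 = 1.85 points and one with mean 11 by 0.27 × 5 × 0.798 = 1.08. That leaves a spurious difference in change of 0.77 points between arms.

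**The case against.** **T0 may be a fresh reading.** It is tempting to infer from Table 4 that the qualifying score is T0, since the table shows one pre-treatment GDS. The inference fails. The Mini-mental State Examination is also an entry criterion and is also absent from Table 4, so the table does not list screening measurements. Each home also waits until it has 26 subjects before moving on, which leaves room for a gap between qualifying and T0. If T0 is new, the within-arm error rate returns to about 0.025 under this model. This stands, and it makes the size of the problem conditional.

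**The hypothesis is between-arm.** A reader might take the maintenance clause as a within-arm claim. In context, the improvements it refers to are those of the combined arm over the two comparators, at follow-up as well as post-intervention. This stands. The fix mostly makes the analysis section say what the Background already implies.

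**The between-arm analysis is already planned, and simple effects normally follow a group-by-time test.** Also true. Nothing in the article says that efficacy will be declared from a within-arm P value, and a usual-care arm that also improved would warn the reader. What remains is that an inferential within-arm test is stated, at the same threshold, with no limit on its use.

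**The size is assumed.** GDS mean and SD are not given, reliability is a lower bound, and a paired t-test is not exactly the five-visit model. A multiplicity correction over visit pairs would lower the rates, but none is stated. These points limit the figures to ranges.

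**Natural course.** One might add that depressive symptoms would improve anyway over the trial period. The article gives no untreated trajectory, so this is not claimed.

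**Conclusion.** The concern holds conditionally and only for the within-arm tests. If the qualifying GDS doubles as T0, an arm in which nothing changes would show a significant fall with probability roughly 0.27–0.74 at reliability 0.73 and 0.16–0.48 at 0.85, for an assumed screened-population mean of 7–11 and SD of 5–6. The chance drops to about 0.08–0.20 where most residents exceed the cut-off, and to the nominal 0.025 if T0 is a separate reading.

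A reader might infer that the trial's main comparison is invalid. The article does not support that: the between-arm contrast serves the stated hypothesis and keeps its error rate under individual randomisation. That protection is not assured if homes, rather than residents, are allocated to interventions, and the article describes both.

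**What to change.** 1. **Statistical analysis.** Report within-group change descriptively, as a mean with confidence interval, without a P value or efficacy claim. Base improvement, and its maintenance to six months, on between-arm GDS differences (group-by-time or baseline-adjusted), including at T4. This costs only wording.
2. **Eligibility and Outcome measures.** State whether T0 is a reading separate from the screening GDS. If it is not, an optional step is to repeat the GDS before session 1, use it as baseline, and keep everyone who qualified whatever the repeat score. This costs one 15-minute questionnaire per resident, and some T0 scores will lie below 11.
3. **Study Design and Randomization and blinding.** Reconcile the two accounts of what is randomised. Regression to the mean can be relied on to cancel between arms only if individuals are randomised, so item 1 gives full protection only in that case.

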### Sample size calculation

Based on a priori power analysis (G-power3.1.9.7) using a power of 0.90 and error probability of 0.05, with a reference to a literature effect size of 0.8 [46, 47], a sample size of 24 participants per group will be needed. Assuming a 10% drop out rate, a sample size of 78 participants will be initially targeted.

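### Repeated-measures ANOVA over five visits is not reconciled with intention-to-treat and uses baseline inefficiently; a baseline-adjusted mixed model on all available follow-up data is the better choice

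*Protocol article*

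**What the plan says.** Under Statistical analysis, the protocol article states that scale scores before and after the intervention, within and between groups, "will be analysed by repeated-measures ANOVA and simple effects analysis if they are normal and have equal variance". The software is SPSS 26.0, and the procedure within it is not named. Skewed measures go to Kruskal–Wallis comparisons. The same paragraph says "Intention-to-treat will be used to process the data". It names no baseline covariate and no treatment of missed visits.

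Study Design and Table 4 give five assessments of every scale, T0 to T4. Sample size calculation works "using a power of 0.90 and error probability of 0.05", "with a reference to a literature effect size of 0.8", and concludes that "a sample size of 24 participants per group will be needed". It then sets the total at 78: "Assuming a 10% drop out rate".

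Two sections describe allocation differently. Study Design divides participants 1:1:1. Randomization and blinding draws envelopes to decide which nursing home delivers which intervention.

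**The concern.** Two features of the named method fit poorly with the rest of the plan.

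First, the classical form of the test needs a complete row of five values for each person. A resident who misses one follow-up visit is lost from the whole analysis, including the visits attended. That sits awkwardly beside an intention-to-treat statement. If those who leave differ in their interim depression scores, the comparison of completers can also be biased.

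Second, the baseline score enters as one of the outcomes and not as a covariate. Comparing change from baseline between arms is less precise than adjusting for baseline. Any group main effect averaged over T0–T4 includes a visit at which treatment can have had no effect. In a trial of 26 per arm, precision that costs nothing to recover is worth recovering.

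**Working it through.** **Inputs from the article:** 5 visits, 24 evaluable per arm (72 in all), 78 recruited, 10% dropout, effect size 0.8, alpha 0.05. **Assumed here:** 0.8 is a standardised mean difference, tests are two-sided, and the baseline-to-follow-up correlation ρ is 0.3, 0.5 or 0.7 (the article gives none).

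**The plan's own figures.** A two-sided t-test at d = 0.8 needs 34 per arm for power 0.90, and 24 per arm gives 0.77. The stated 24 is therefore not reproduced under these readings. That is a separate matter; 24 is used below only as the plan's evaluable number. For dropout, 72 / 0.9 = 80, close to the stated 78.

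**Complete cases.**
- 10% dropout: 78 × 0.90 = 70.2, about 70, against 72 required.
- 5% missing independently at each of four follow-up visits (assumed): 78 × 0.95⁴ = 63.5, about 64.
- 10% missing independently at each (assumed): 78 × 0.90⁴ = 51.2, about 51.

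**Baseline as a repeated measure or as a covariate.** For one pairwise contrast at one visit, with outcome SD 1:
- change from baseline has SD √(2(1−ρ)), so the effective d is 0.8 / √(2(1−ρ));
- baseline adjustment has residual SD √(1−ρ²), so the effective d is 0.8 / √(1−ρ²);
- the variance ratio is 2(1−ρ)/(1−ρ²) = 2/(1+ρ).

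Noncentral t, 24 per arm:

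| ρ | effective d, change | power | effective d, adjusted | power | variance ratio |
|---|---|---|---|---|---|
| 0.3 | 0.676 | 0.63 | 0.839 | 0.81 | 1.54 |
| 0.5 | 0.800 | 0.77 | 0.924 | 0.88 | 1.33 |
| 0.7 | 1.033 | 0.94 | 1.120 | 0.97 | 1.18 |

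**Dilution of a group main effect.** Suppose one of three arms is better by 0.8 SD at T1–T4. The SD of the arm means is 0.8 × √2/3 = 0.377. Averaging in T0, where the difference is nil, multiplies this by 4/5, giving 0.302. With N = 72 and ρ = 0.7, the noncentrality is f² × N × m / (1 + (m−1)ρ):
- T1–T4 (m = 4): 0.377² × 288 / 3.1 = 13.2, power 0.90.
- T0–T4 (m = 5): 0.302² × 360 / 3.8 = 8.6, power 0.73.

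This applies only if the group main effect is the test. The article does not say which effect is.

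**The case against.** The strongest reply is that nothing here is a contradiction. Intention-to-treat also means analysing people in the arm to which they were allocated, and a condensed article may leave an imputation rule to the full protocol or analysis plan. That stands: a reader might infer that the analysis contradicts intention-to-treat, but the text supports only that the two statements are not reconciled.

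The sample size already allows for 10% dropout, so falling to 70 is close to what was budgeted; the gap to 72 arises because 78 was used in place of 80. That also stands. The larger losses come from missed single visits, whose rate the article does not give.

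A reader might infer that including T0 biases the result. Under individual randomisation it does not bias the group-by-time test, which already uses baseline. The gain also shrinks as ρ rises. The article quotes a GDS retest reliability above 0.73; at ρ = 0.73 the comparison is 0.96 vs 0.98. However, retest reliability is not the correlation across an intervention and six months, and entry at GDS ≥ 11 truncates baseline, which tends to lower the correlation.

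Two further inferences lack support. The Social engagement section says "The purpose of assessing social engagement in this study is to avoid confounding the effects of social engagement and reminiscence therapy", which might suggest adjustment for post-treatment engagement. Statistical analysis specifies no such adjustment, and the Abstract lists social engagement as a secondary outcome. Treatment in subgroups of 6–7 might suggest an inflated type I error, but any figure would rest on an intraclass correlation that the article does not give.

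**Conclusion.** The point holds as a weakness of method, not as a proven contradiction. Without imputation, the named analysis keeps about 70 of 78 participants at the expected dropout, and fewer if single visits are missed. Against baseline adjustment it gives up about 18 percentage points of power at ρ = 0.3, 11 at 0.5 and 3 at 0.7 for a single pairwise contrast at one visit. A main effect that includes T0 would lose more: 0.90 to 0.73 in the case worked above. The size therefore depends on a correlation, a missed-visit pattern and a choice of test that the article does not give. Possible bias from analysing completers is real in principle, but the article offers nothing from which to size it.

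All the power figures presume individual randomisation. If whole homes are allocated, one per arm, they do not apply: arms may differ at T0, and home is fully confounded with treatment whatever model is used.

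**What to change.** First reconcile Study Design with Randomization and blinding on the unit of allocation. The model below answers the trial's question only if individuals are randomised.

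Then replace the repeated-measures ANOVA for the primary outcome with a linear mixed model for GDS at T1–T4:
- fixed effects for arm, visit, arm-by-visit and T0 GDS;
- unstructured within-person covariance and a small-sample degrees-of-freedom correction;
- all available follow-up data, with each participant in the allocated arm.

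State the visit and contrast that carry the primary conclusion.

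The cost is a change of wording and slightly more modelling work. SPSS MIXED fits such models, and no extra participants or visits are needed. The model relies on data being missing at random. Participants with no post-baseline visit still contribute nothing, unless T0 is kept as an outcome in a constrained-baseline model or values are imputed; the plan should say which. If repeated-measures ANOVA is retained, the minimum is to state how missed visits are handled under intention-to-treat.
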